## Background

Substance use disorders and personality disorders often co-occur [1,2]. Patients with personality disorders are commonly seen in treatment programs for substance abuse, consume a disproportionate amount of staff time, and are more likely to drop out from substance abuse treatment interventions [3,4].

At the same time, therapists and other professionals tend to react negatively to patients with personality disorders at an emotional level [5], this is especially the case with cluster B (dramatic/erratic) personality disorders [6].

Even if patients with personality disorders benefit from treatment, they often remain more symptomatic than patients without personality disorders, and remain at a lower level of functioning [7,8].

Therefore, treatment that meets the needs of patients with substance abuse and personality disorders is needed. Recently, some studies have shown that integrated treatment for personality disorders and substance abuse may be superior to treatment that focuses solely on substance abuse treatment [9-11].

This randomized experimental study is designed to assess whether systematic assessment of personality disorders improves outcomes, vs. assessment of Axis I disorders alone.

The objective of this study is to estimate the effect of routine assessment of co-morbid axis II disorders in a centralized intake unit for substance use disorders.

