### Baseline interview

At the baseline interview, the interviewer informs the patient of the study, and explains that the study focuses of psychological and behavioural problems that people with substance abuse regularly encounter. He then explains that there are two different interviews, and that patients will be randomly assigned to one of two types. If asked, he will explain that he does not yet know what kind of interview he will conduct the second time they meet, but he will give a further explanation at their second appointment. If the patient gives consent to participate in the study, a brief structured assessment of axis I disorders is conducted. The assessment is kept brief, in order to reduce assessment reactivity, i.e., the effects that assessment can have on treatment outcomes [20].

The instruments used are therefore chosen to be brief, but have strong indications of validity:

• Anxiety/depression is assessed with The Kessler 6 interview [14].

• Attention Deficit/Hyperactivity Disorder is assessed with the Adult ADHD Self-Report Scale [14].

• Illicit substance dependence and alcohol dependence are both assessed by means of the Opiate Treatment Index substance use items [15].

• Severity of alcohol and illicit drug dependence will be assessed by the Severity of Dependence Scale [SDS] [21].

• Personality disorder severity is assessed with the Structured Assessment of Personality – Abbreviated Scale [SAPAS] [22,23].

If the patient does not speak Danish or English well, does not screen positive for substance dependence as indicated by an SDS score of 3 or more for either alcohol or drugs, a feedback session is scheduled, and the patient is informed that based on his data, we wish to give him individual feedback on the next session.

If the patient satisfies inclusion criteria (speaks Danish or English; SDS > 3; gives informed consent), a second interview is scheduled. The interviewer will also schedule a meeting with the researcher conducting follow-up interviews.

The patient is then randomized to either experimental or control conditions.

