### Outcome evaluation

A single measure of outcome will be used as the primary outcome measure: The proportion of areas in which a 30% reduction occurred at each follow-up wave (K6, WSAS, and OTI substance use). This measure can theoretically range from -3 (deterioration in all areas) to +3 (improvement in all areas.

The data will be analyzed with mixed effects ordinal regression, using baseline values of the three outcome measures as covariates [30].

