### Risks and anticipated benefits for trial participants and society, including how the benefits justify the risks

Patients with substance use disorders and co-morbid personality disorder experience a number of serious problems. Patients with co-morbid personality disorder tend to remain symptomatic long after treatment [7,8], and patients with some co-morbid personality disorders tend to commit a substantial amount of the crime that substance abusers commit [31].

If the findings of this study show that personality assessment can significantly improve the functioning of patients with substance use disorders, this can have significant impacts on both the quality of life of patients, and on society.

The main risk of this study is that patients experience a worsening of psychiatric symptoms or substance use as a reaction to receiving a feedback concerning their own personal functioning. There is some indication that symptoms may fail to improve with focus on personality, even if this focus improves substance use and therapeutic alliance [9]. We will monitor psychiatric symptoms every 3 months during the study, and patients have access to caseworker, psychiatrist and psychologist at the treatment centre.

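### The primary model's stated covariates leave out baseline SAPAS, which every patient has before randomisation; adding it is a free improvement worth a small gain in power

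*Protocol article*

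**What the plan says.** The Outcome evaluation section of the protocol article gives the model and its covariates. "The data will be analyzed with mixed effects ordinal regression", "using baseline values of the three outcome measures as covariates". The three measures named there are the K6, the WSAS and OTI substance use.

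The Baseline interview section adds a further measure: "Personality disorder severity is assessed with the Structured Assessment of Personality" – Abbreviated Scale (SAPAS). Table 1 also marks SAPAS at baseline. Allocation comes at the end of that section, after the baseline instruments: "The patient is then randomized to either experimental or control conditions".

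On prognosis, the Background says that patients with personality disorders "are more likely to drop out from substance abuse treatment interventions" and that, even when treatment helps, "they often remain more symptomatic than patients without personality disorders" and function at a lower level. The section on risks and anticipated benefits repeats the point: "Patients with co-morbid personality disorder tend to remain symptomatic long after treatment".

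The objective in the Background is "to estimate the effect of routine assessment of co-morbid axis II disorders" at a central intake unit. Personality disorder is not an inclusion criterion.

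**The concern.** The trial tests an intervention built around personality disorder. It measures the severity of that condition in everyone before allocation and describes the condition as prognostic for symptoms and functioning. Symptoms (K6) and functioning (WSAS) are two of the three components of the outcome. A model that lists its covariates and leaves this one out gives up precision that the data already collected could supply.

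Two things are at stake. One is a modest amount of power. The other is pre-specification: if SAPAS were added only after results are known, the estimate itself would move, and the choice would be open to criticism.

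**Working it through.** The article states no sample size, power, effect size or SAPAS correlation, so there is no figure of its own to reproduce. The check has three steps.

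**1. Is SAPAS a legitimate covariate?** It is part of the baseline interview for all patients, and randomisation follows that interview. It is therefore a pre-randomisation variable available in both arms. The full axis II interview takes place after randomisation and in the experimental arm only, so its diagnoses could not serve this purpose. SAPAS is the only baseline personality-disorder measure listed for both arms.

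**2. What would adding it gain?** Let r be the partial correlation of SAPAS with outcome, given the baselines of the K6, WSAS and OTI. This is an assumption, with range 0.1 to 0.3; three baselines are already in the model, so larger values would be generous. In a linear model the residual variance is multiplied by 1 − r², and the equivalent gain in sample size is 1/(1 − r²) − 1.

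- r = 0.1: 1 − 0.01 = 0.99; gain 1/0.99 − 1 = 1.0%
- r = 0.2: 1 − 0.04 = 0.96; gain 1/0.96 − 1 = 4.2%
- r = 0.3: 1 − 0.09 = 0.91; gain 1/0.91 − 1 = 9.9%

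This is only an approximation for the stated model. In a logit-type ordinal regression a prognostic covariate does not simply shrink a residual variance. The conditional treatment effect also changes size, so adjusted and unadjusted estimates are different quantities.

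**3. How precise would an arm-by-SAPAS contrast be?** Simplify SAPAS to two groups, with a share p in the higher-severity group. The number per arm needed to detect a difference of size d between the two groups' treatment effects is 2(z_α + z_β)²(1/p + 1/(1 − p))/d². A main effect of the same size d needs 2(z_α + z_β)²/d². The ratio is 1/p + 1/(1 − p).

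- p = 0.4 or 0.6: 2.50 + 1.67 = 4.17
- p = 0.8: 1.25 + 5.00 = 6.25

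The values of p are assumed. Such a contrast would need about four to six times the sample of a main effect of the same size. A continuous SAPAS term would not follow this ratio exactly, but it too should be expected to be imprecise.

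**The case against.** The strongest reply is that nothing here is wrong. Adjusting for the baselines of the outcome components is standard, the comparison is valid under randomisation, and one more covariate is a matter of preference. That stands, and it is why the point is an improvement and not a defect.

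Other parts of the reply also stand:

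- The article calls personality disorder prognostic, not the SAPAS score. The link rests on its description of SAPAS as the severity measure.
- Drop-out from treatment is not part of the outcome in the Outcome evaluation section. Remaining more symptomatic describes level, which the baseline covariates partly absorb, whereas the outcome is built on relative change. Both points argue for a small r.
- Randomisation is stratified by characteristics that are withheld on purpose. They could include SAPAS, and the article does not say whether they enter the model.

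A reader might go further and infer that no modifier analysis is planned. The article does not show this: secondary interactions are commonly left to a full protocol or analysis plan, neither of which is at hand.

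A reader might also infer that the overall effect is diluted by patients with no personality disorder to report on, so that a null result could not be interpreted. Diagnostic feedback is indeed given per positive result, and only the experimental arm has axis II results. But every experimental patient receives the personality-disorder description and interview, and every control has a different interview, which is summarised in the feedback. An effect in patients without a disorder is therefore not excluded, and any dilution figure would have to assume that it is zero. Moreover, the average over all intake patients is the stated target, so a null would still answer the question asked.

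The reply does not remove the fact that the article states its covariates and omits an available baseline measure of the condition under study.

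**Conclusion.** The point holds as a free improvement. The stated covariate set omits a baseline measure that is already collected, precedes randomisation and is plausibly prognostic. The cost of omitting it is some power, roughly equivalent to 1% to 10% more patients. That range rests on an assumed partial correlation of 0.1 to 0.3 and on a linear-model approximation to an ordinal analysis. Omission introduces no bias, and the all-comer analysis matches the objective. The interaction is only an optional addition.

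**What to change.** In the Outcome evaluation section, add the baseline SAPAS total to the covariates of the primary model, and keep all randomised patients as the primary population. Fix this before outcome data are examined by arm, because the adjusted effect in an ordinal model differs in size from the unadjusted one.

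Optionally, and only if the full plan does not already contain it, name arm by continuous baseline SAPAS as one secondary, exploratory contrast, to be read alongside the overall effect. State that it will be imprecise. Use SAPAS for this and not the axis II diagnoses, which controls do not have.

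The cost is one covariate, plus one extra term in a secondary model if the option is taken. No new data are needed.

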### Risks and anticipated benefits for trial participants and society, including how the benefits justify the risks

Patients with substance use disorders and co-morbid personality disorder experience a number of serious problems. Patients with co-morbid personality disorder tend to remain symptomatic long after treatment [7,8], and patients with some co-morbid personality disorders tend to commit a substantial amount of the crime that substance abusers commit [31].

If the findings of this study show that personality assessment can significantly improve the functioning of patients with substance use disorders, this can have significant impacts on both the quality of life of patients, and on society.

The main risk of this study is that patients experience a worsening of psychiatric symptoms or substance use as a reaction to receiving a feedback concerning their own personal functioning. There is some indication that symptoms may fail to improve with focus on personality, even if this focus improves substance use and therapeutic alliance [9]. We will monitor psychiatric symptoms every 3 months during the study, and patients have access to caseworker, psychiatrist and psychologist at the treatment centre.

### Ethical approval

Institutional Review Boards in Denmark do not approve or disapprove of trials or other studies of psychosocial interventions. The medical director of social medicine in the City of Copenhagen, M.D. [name], read and approved the protocol in Danish. Patients will be given full information about the nature of the study, and be asked to give informed consent. Patients who refuse participation in the study will be given full access to all regular treatment services in the organisation, similar to the control group.

Ethically, the issues related to this study concerns the consequences of receiving serious diagnoses for which there is no clear and simple treatment, in particular personality disorders. However, although there is no simple treatment, patients are given suggestions and support, and have access to the support of the treatment centres

When patients in this trial are assessed, they also receive feedback and advice about how to handle the issues involved, and their caseworkers are given feedback and advice on how to best support patients.

## Discussion

This paper describes the study protocol of a randomized controlled trial concerning personality disorder assessment and feedback versus an open interview. The aim of this study is to assess the potential value of personality disorder assessment for referral and casework in a real-life setting. The study design described above has specific strengths and limitations.

The study has a single-blind design, where patients are unaware if their treatment is designated as an "experimental" or "control" treatment. Follow-up interviewers are blinded to allocation, and we have procedures to reduce the risk that follow-up interviewers are made aware of subjects' status (i.e., follow-up interviewers make contact with patients before randomization is known; patients are told not to disclose details about the interview to the follow-up interviewers).

The study uses an attention placebo design, which means that the effects of time and attention are controlled for. Research has shown strong assessment reactivity in substance use outcome [20], meaning that patients who are exposed to assessment show improvement only for that reason. The amount of contact is controlled for in this trial. This means that if significant effects are found, they give strong support to the efficacy of personality disorder assessment.

The setting in which the study takes place is a community service. This means that although training and supervision is provided for caseworkers, the caseworkers are not primarily working with the research project. While this may reduce the potential efficacy of the intervention, it means that the study is in a sense between an efficacy trial and an effectiveness study.
